### Objectives

The aim of the FURTHER trial is to evaluate the effectiveness and cost-effectiveness of MR-HIFU (alone or in combination with EBRT) compared to EBRT alone for palliation of CIBP. The primary endpoint of this trial is patient-reported pain response 14 days after the start of treatment (Table 1). As MR-HIFU has been shown to be particularly fast acting (within 3 to 7 days [14–21]), compared to EBRT (4–6 weeks [6–8]). It is expected that patients suffering from cancer-induced bone pain could mainly benefit from MR-HIFU in the early weeks after treatment. Therefore, the primary endpoint was set at 14 days.

**Table 1 Tab1:** Primary and Secondary outcomes of the FURTHER-trial, a trial looking at the impact of treatment with MR-HIFU with or without radiotherapy on patients with painful bone metastases

**Primary outcomes**	
1.1. Pain response 14 days after completion of treatment	Assessed using the BPI and patient pain diary. Used to assess the short-term effectiveness of treatment
1.2. Pain response at 14 days after inclusion	Assessed using the BPI and patient pain diary. Used to assess the effectiveness of treatment taking hospital logistics and planning into account

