**Methods/design:**

The FURTHER trial is an international multicenter, three-armed randomized controlled trial. A total of 216 patients with painful bone metastases will be randomized in a 1:1:1 ratio to receive EBRT only, MR-HIFU only, or combined treatment with EBRT followed by MR-HIFU. During a follow-up period of 6 months, patients will be contacted at eight time points to retrieve information about their level of pain, QoL, and the occurrence of (serious) adverse events. The primary outcome of the trial is pain response at 14 days after start of treatment. Secondary outcomes include pain response at 14 days after trial enrolment, pain scores (daily until the 21st day and at 4, 6, 12 and 24 weeks), toxicity, adverse events, QoL, and survival. Cost-effectiveness and cost-utility analysis will be conducted.

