**Secondary outcomes**	
2.1. Patient-reported pain scores	Assessed using the BPI and patient pain diary during the first 21 days, at 4 and 6 weeks and 3 and 6 months following treatment
2.2. Physician reported toxicity	Assessed by telephone call at 3 days; 1, 4, and 6 weeks; and 3 and 6 months following completion of treatment according to the Common Terminology Criteria for Adverse Events (CTCAE) version 5.0
2.3. Patient-reported quality of life	Assessed using the EORTC QLQ BM22, C15-PAL, EQ-5D-5L, and PGIC at baseline; 1, 2, and 4 weeks; and 3 and 6 months following completion of treatment
2.4. Local tumor control	Assessed using CT and/or MRI imaging at patient discretion at 3 and/or 6 months after completion of treatment
2.5. Levels of anxiety and depression	Assessed among patients, patients’ partners, and caregivers by the Hospital Anxiety and Depression Scale (HADS) and EDIZ-list at baseline; 1, 2, 4, and 6 weeks; and 3 and 6 months following completion of treatment
2.6. Cost-effectiveness of the treatment	Assessed as cost per responder and cost per quality-adjusted life years (QALY), from a payer perspective, at 6 months of follow-up

Pain response will be based on the numeric rating scale (NRS) and the pain severity index calculated from the Brief Pain Inventory (BPI) questionnaire [28, 29]. In addition, analgesic and anti-neuropathic drug use is recorded, and all opioid analgesics are expressed as the oral morphine equivalence dose (OMED). The primary endpoint of the trial will follow the International Consensus on Palliative Radiotherapy Endpoints for Future Clinical Trials in Bone metastases [30]. In accordance with the consensus, pain will be assessed by the worst pain score over the previous 3 days. Patients will be categorized as responders when either a reduction of pain score of at least 2 points without increase of analgesic intake is achieved, or a reduction of analgesic intake of at least 25% is accomplished without an increase of pain score at the treated site. All other patients will be categorized as non-responders.

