^***^As judged by the operator, e.g., nerve bundles, skin, extensive scarring, non-targeted bones, air (e.g., hollow viscera), and (external) fixation device

*ECOG* Eastern Cooperative Oncology Group, *KPS* Karnofsky Performance Score, *HIFU* high-intensity focused ultrasound, *EBRT* external beam radiotherapy

Given the urgent need for rapid pain relief, patients will be allowed to make a decision for participation in the study and sign an informed consent immediately after receiving the information. The researcher will randomize the patient using the online Castor EDC database [27]. The treatment arm allocation will immediately be shown. Patients will be treated according to the treatment arm they are assigned to.

To retrieve information about their level of pain, QoL, and (serious) adverse events, patient outcome measures will be assessed at several time points during a follow-up period of 6 months (Table 3). Starting on the treatment day, a paper-based patient diary will be used for self-reporting of pain levels and pain medication use during the first 21 days following the start of treatment, and at 1, 3, and 6 months. The paper diary and questionnaires will be supplied and explained to patients prior to the treatment. Furthermore, patients will also be interviewed or contacted by telephone at baseline, and at 1, 2, 4, and 6 weeks and 3 and 6 months to assess pain response, patient-reported QoL, and (serious) adverse events. A schematic overview of the follow-up timelines for each randomization arm is illustrated in Fig. 2. The paper-based diary and questionnaires are collected by the local partner institutions and entered into the web-based central Castor EDC database. A data management plan is in place to ensure data quality and a dedicated data-management team located at the UMC Utrecht will ensure data security, coding, and storage. Quality and completeness of data will be monitored by an independent team of trained data monitors.

**Table 3 Tab3:** Follow-up timeline in the FURTHER trial

	Ti	T0	T1	T2	T3	T4	T5	T6	T7	T8
	Incl	Tx	3d	7d	14di	14d	4w	6w	3 m	6 m
Informed consent	**x**									
Baseline data	**x**									
Patient diary *		**x**	**x**	**x**	**x**	**x**				
Brief Pain Inventory	**x**						**x**	**x**	**x**	**x**
Assessment of adverse events (by telephone)			**x**	**x**	**x**	**x**	**x**	**x**	**x**	**x**
Quality of life questionnaires **		**x**		**x**		**x**	**x**	**x**	**x**	**x**

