### Sample size calculation

The study is powered to detect a difference in proportions of patients with pain response of the treated bone metastasis at 14 days after the start of treatment. For this purpose, the two MR-HIFU arms will be combined, and the sample size will be determined on a 2:1 comparison. We calculated we need 72 patients in each arm to achieve a power of 90%, using a one-sided alpha of 5% and assuming a 10% post-randomization dropout using R version 4.0.4 (R foundation for statistical computing; https://R-project.org/). We assume that the response rates during this trial will be similar to previous studies. Therefore, we base this calculation on previous research showing that the proportion of patients with successful pain palliation at 14 days following the start of treatment is 0.69 for MR-HIFU and 0.40 for EBRT [9, 14]. We conservatively assume that 10% of patients allocated to one of the MR-HIFU arms will not be able to undergo MR-HIFU and will therefore receive EBRT.

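### Table 1 counts the primary endpoint's 14 days from completion of treatment, while the abstract, Objectives, sample size and analysis sections count from its start; following Table 1 would make the assessment day depend on arm and fractionation

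*Protocol article*

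**What the plan says.** The protocol article gives the primary endpoint two time origins.

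- **Completion.** Table 1, row 1.1: "1.1. Pain response 14 days after completion of treatment".
- **Start.** The abstract: "The primary outcome of the trial is pain response at 14 days after start of treatment". Objectives: "The primary endpoint of this trial is patient-reported pain response 14 days after the start of treatment (Table 1"; that sentence cites the very table that says otherwise. The sample size section powers the trial on a "difference in proportions of patients with pain response of the treated bone metastasis at 14 days after the start of treatment". The statistical analysis section compares baseline with 14 days from the start.

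The Objectives section also refers the reader to Table 1 for the full list of endpoints, so the table cannot be set aside as a loose summary. Nor is row 1.1 the only place with the completion wording: rows 2.2 to 2.5 use it too. By contrast, the Objectives text times quality of life from the start of treatment, and the analysis section times both toxicity and quality of life from the start.

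On data capture, the patient diary runs "during the first 21 days following the start of treatment" (Patient selection and follow-up), and the Fig. 2 caption starts follow-up after the first session in all three arms. The Table 3 footnote on the diary says only that the 21 days come after treatment, without naming an origin.

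**The concern.** The two origins coincide only when treatment is a single session. MR-HIFU alone is one session, but EBRT may take 1, 5, 6 or 10 fractions, and the length of combined treatment varies with fractionation and MR-HIFU availability. On the completion clock, the time from first treatment to read-out would therefore depend on arm and schedule.

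That matters more here than in most trials. The Objectives section justifies the 14-day endpoint by speed: MR-HIFU is said to act within 3 to 7 days and EBRT within 4 to 6 weeks. A later read-out gives EBRT more time to work and so changes the contrast the trial was designed to measure. It would also break the link to the planning response rates (0.69 for MR-HIFU, 0.40 for EBRT), which the sample size section states at 14 days from the start.

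**Working it through.** **Inputs** (all from the protocol article)

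- EBRT schedules: 1, 5, 6 or 10 fractions, one per day, five days a week (Radiotherapy treatment).
- MR-HIFU: one session (MR-HIFU treatment).
- Combined arm: EBRT followed by MR-HIFU (abstract); length depends on fractionation and MR-HIFU availability (Combined treatment).
- Diary: 21 days from the start (Patient selection and follow-up).

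**The plan's own day.** On the start clock the assessment is day 0 + 14 = day 14 for every arm and schedule. This agrees with the planning rates and lies inside the diary.

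**The Table 1 day.** Let the first session be day 0, n the number of fractions, and s the starting weekday (Monday = 0 to Friday = 4). Assume weekday treatment with no missed days or public holidays.

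- Day of last fraction: L = (n − 1) + 2 × floor((s + n − 1)/5), where the second term counts the weekends crossed.
- Assessment day: D = L + 14.

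| Treatment | L | D = L + 14 | Days later than MR-HIFU alone | Diary counted from start |
|---|---|---|---|---|
| MR-HIFU alone | 0 | 14 | 0 | inside |
| EBRT, 1 fraction | 0 | 14 | 0 | inside |
| EBRT, 5 fractions | 4 + 0 = 4 (Monday start) or 4 + 2 = 6 | 18 or 20 | 4 or 6 | inside |
| EBRT, 6 fractions | 5 + 2 = 7 (any start) | 21 | 7 | at its edge |
| EBRT, 10 fractions | 9 + 2 = 11 (Monday start) or 9 + 4 = 13 | 25 or 27 | 11 or 13 | outside |
| Combined | at least the L of its EBRT schedule | at least that schedule's D | at least that schedule's excess | depends on schedule |

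**Combined arm.** If MR-HIFU falls m days after the last fraction, D = L + m + 14. The article gives no value for m, so only the lower bound (m = 0) can be stated.

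**Nearest later pain record for 10 fractions.** If the 4-week BPI is counted from the start, it falls on day 28, which is 28 − 27 = 1 or 28 − 25 = 3 days after the Table 1 day.

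**Average shift.** This is not computable, because the mix of schedules is not given. Per patient it runs from 0 to 13 days for EBRT, and can be longer in the combined arm.

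**Sample size.** The rates that enter it are already stated at 14 days from the start, so settling on the start clock changes nothing there.

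**The case against.** The best reply is that the operative parts of the plan agree. The abstract, Objectives, sample size and analysis sections use the start clock, and so do the diary description and the Fig. 2 caption. On that reading everyone is assessed on day 14, the planning rates fit and the diary covers the day. This stands, and it makes the harm conditional on someone following Table 1. It does not remove the contradiction, because Objectives sends the reader to Table 1 for the endpoints and the completion wording recurs in further rows.

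Several stronger readings are tempting but not supported:

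- **That the arms will in fact be read on different days, or that the analyst is free to pick a clock after seeing the data.** The analysis section states one clock, the start.
- **That 10-fraction patients would have no usable pain record.** The text counts the diary from the start, but the Table 3 footnote leaves the origin open; a diary run from completion would cover the day. Even on the start count, a BPI could follow within 1 to 3 days.
- **That the combined arm would be delayed by a known amount.** The article asks for both treatments preferably within a week of inclusion and gives no interval between them.
- **That there are two competing primary pain scales.** The article says "Pain response will be based on the numeric rating scale (NRS) and the pain severity index calculated from the Brief Pain Inventory (BPI"), but it then ties the primary endpoint to the international consensus, under which "pain will be assessed by the worst pain score over the previous 3 days". The natural reading is that the first sentence names instruments and the second fixes the score.

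Stratification by planned fractionation should balance schedules across arms. It cannot close the gap to MR-HIFU alone, which has no fractions.

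**Conclusion.** The contradiction is real, lies in the current text and concerns the primary endpoint; the article reports no amendments that could explain it. Table 1 states a different rule from the one that was powered and is to be analysed. If Table 1 were followed, the read-out would range from day 14 to day 27 after the start across the single-modality arms, giving multi-fraction EBRT up to 13 more days than MR-HIFU alone. It would no longer correspond to the 0.40 and 0.69 rates. For 10 fractions it would fall after a 21-day diary counted from the start.

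These days assume weekday fractions without interruption. The effect on the response proportions cannot be estimated, because the article gives neither the fractionation mix nor response rates by day. Nothing here shows that the trial is being run on the completion clock, and the sample size is not affected.

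**What to change.** 1. Change Table 1, row 1.1, to: *Pain response 14 days after start of treatment (first session)*.
2. Reconcile the completion wording for toxicity and quality of life (rows 2.2 and 2.3) with the start clock that the analysis section uses for both, and that the Objectives text also uses for quality of life. The analysis section gives no start clock for local control or for anxiety and depression (rows 2.4 and 2.5), so no contradiction with it arises there.
3. As a minor clarification only, say that the 2-point response criterion uses the worst pain score over the previous 3 days, as the article already says for the primary endpoint.

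The cost is a change of wording. It needs no new data, visits or patients.

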**Secondary outcomes**	
2.1. Patient-reported pain scores	Assessed using the BPI and patient pain diary during the first 21 days, at 4 and 6 weeks and 3 and 6 months following treatment
2.2. Physician reported toxicity	Assessed by telephone call at 3 days; 1, 4, and 6 weeks; and 3 and 6 months following completion of treatment according to the Common Terminology Criteria for Adverse Events (CTCAE) version 5.0
2.3. Patient-reported quality of life	Assessed using the EORTC QLQ BM22, C15-PAL, EQ-5D-5L, and PGIC at baseline; 1, 2, and 4 weeks; and 3 and 6 months following completion of treatment
2.4. Local tumor control	Assessed using CT and/or MRI imaging at patient discretion at 3 and/or 6 months after completion of treatment
2.5. Levels of anxiety and depression	Assessed among patients, patients’ partners, and caregivers by the Hospital Anxiety and Depression Scale (HADS) and EDIZ-list at baseline; 1, 2, 4, and 6 weeks; and 3 and 6 months following completion of treatment
2.6. Cost-effectiveness of the treatment	Assessed as cost per responder and cost per quality-adjusted life years (QALY), from a payer perspective, at 6 months of follow-up

Pain response will be based on the numeric rating scale (NRS) and the pain severity index calculated from the Brief Pain Inventory (BPI) questionnaire [28, 29]. In addition, analgesic and anti-neuropathic drug use is recorded, and all opioid analgesics are expressed as the oral morphine equivalence dose (OMED). The primary endpoint of the trial will follow the International Consensus on Palliative Radiotherapy Endpoints for Future Clinical Trials in Bone metastases [30]. In accordance with the consensus, pain will be assessed by the worst pain score over the previous 3 days. Patients will be categorized as responders when either a reduction of pain score of at least 2 points without increase of analgesic intake is achieved, or a reduction of analgesic intake of at least 25% is accomplished without an increase of pain score at the treated site. All other patients will be categorized as non-responders.

### Patient selection and follow-up

The study population will consist of male and female adults (age ≥ 18 years) with non-vertebral painful bone metastases that are accessible for MR-HIFU and EBRT who are able to give a written informed consent. Patients will be enrolled at the departments of Radiation Oncology of all participating centers. The radiation oncologist will approach potentially eligible patients who meet the in- and exclusion criteria for study participation (Table 2). (S)he will shortly explain the study (design) and the three treatment strategies (EBRT only, MR-HIFU only, or combined EBRT and MR-HIFU). When patients express interest, they will receive more detailed information about the study. The investigator or an authorized delegate will check with patients whether they have understood the aim and content of the study. Then, patients will be requested to sign a written informed consent.

**Table 2 Tab2:** Inclusion and exclusion criteria of the FURTHER trial

Inclusion criteria	Exclusion criteria
Age ≥ 18 years	Previous surgery on the target location
Patient capable of giving informed consent	Neurological symptoms due to nerve involvement of target lesion
Referral to radiotherapy department due to painful metastatic bone lesion (NRS ≥ 4)	Need for surgery of targeted location due to (impending) pathological fracture
Pain from the target lesion is distinguishable from other lesions *	Unavoidable critical structures or dense tissues in the target area ***
Target lesion location is accessible for MR-HIFU and EBRT **	Curative intention of treatment plan
Target lesion is visible on pre-treatment MR or CT imaging, with a maximum diameter of 8 cm	Contraindications MRI or sedation
Participant able to fit in the MRI gantry	Participant enrolled in another clinical interventional study related to bone metastases treatment or pain relief treatment
Reasonable performance score (KPS ≥ 50% or Zubrod/ECOG/WHO < 3)	Clinically relevant medical history or physical findings that could interfere with the patient's safety as judged by the treating physician
Life expectancy ≥ 3 months	

^*^Solitary painful metastatic bone lesion or multiple metastatic lesions with one predominantly painful target lesion (≥ 2 points higher pain score than other lesions)

^**^For example, extremities, pelvis (os pubis, os ilium, os ischium, sacrum, acetabulum), shoulders, in selected cases ribs and sternum (if no lung tissue in HIFU beam path)

^***^As judged by the operator, e.g., nerve bundles, skin, extensive scarring, non-targeted bones, air (e.g., hollow viscera), and (external) fixation device

*ECOG* Eastern Cooperative Oncology Group, *KPS* Karnofsky Performance Score, *HIFU* high-intensity focused ultrasound, *EBRT* external beam radiotherapy

Given the urgent need for rapid pain relief, patients will be allowed to make a decision for participation in the study and sign an informed consent immediately after receiving the information. The researcher will randomize the patient using the online Castor EDC database [27]. The treatment arm allocation will immediately be shown. Patients will be treated according to the treatment arm they are assigned to.

To retrieve information about their level of pain, QoL, and (serious) adverse events, patient outcome measures will be assessed at several time points during a follow-up period of 6 months (Table 3). Starting on the treatment day, a paper-based patient diary will be used for self-reporting of pain levels and pain medication use during the first 21 days following the start of treatment, and at 1, 3, and 6 months. The paper diary and questionnaires will be supplied and explained to patients prior to the treatment. Furthermore, patients will also be interviewed or contacted by telephone at baseline, and at 1, 2, 4, and 6 weeks and 3 and 6 months to assess pain response, patient-reported QoL, and (serious) adverse events. A schematic overview of the follow-up timelines for each randomization arm is illustrated in Fig. 2. The paper-based diary and questionnaires are collected by the local partner institutions and entered into the web-based central Castor EDC database. A data management plan is in place to ensure data quality and a dedicated data-management team located at the UMC Utrecht will ensure data security, coding, and storage. Quality and completeness of data will be monitored by an independent team of trained data monitors.

**Table 3 Tab3:** Follow-up timeline in the FURTHER trial

	Ti	T0	T1	T2	T3	T4	T5	T6	T7	T8
	Incl	Tx	3d	7d	14di	14d	4w	6w	3 m	6 m
Informed consent	**x**									
Baseline data	**x**									
Patient diary *		**x**	**x**	**x**	**x**	**x**				
Brief Pain Inventory	**x**						**x**	**x**	**x**	**x**
Assessment of adverse events (by telephone)			**x**	**x**	**x**	**x**	**x**	**x**	**x**	**x**
Quality of life questionnaires **		**x**		**x**		**x**	**x**	**x**	**x**	**x**
Anxiety and depression in patient/partner/caregiver (HADS + EDIZ)		**x**		**x**		**x**	**x**	**x**	**x**	**x**
Patient Global Impression of Change score				**x**	**x**	**x**	**x**	**x**	**x**	**x**
CT and/or MRI ***		**x**							**x**	**x**

^*^First 21 days after treatment. Contains daily BPIs and weekly PROMs

^**^EORTC QLQ BM22, EORTC QLQ C15-PAL, EQ-5D-5L

^***^At the patient discretion

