### Intervention allocation

Randomization will be done centrally with a computer-generated sequence in Castor EDC [27]. Variable block randomization will be applied as allocation concealment mechanism. Randomization is stratified by institution and planned EBRT fractionation schedule. Patients and doctors will not be blinded to treatment and treatment allocation will not be concealed. Concealment of treatment allocation is not possible due to the evident differences between both MR-HIFU and EBRT interventions. Randomization will be performed during or after physical consultation on the Radiotherapy Department. Shortly after randomization, the patients will be informed about the randomization outcome and randomization arm-specific procedures, and treatment preparations will be started.

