### Statistical analysis

All statistical analyses will be performed using IBM SPSS statistics, version 24 (IBM Corp. Armonk, NY, USA) and R version 4.0.4 (R foundation for statistical computing; https://R-project.org/). Data characterized by normal distribution will be expressed as means with standard deviations. Parameters not normally distributed will be expressed as medians with the interquartile ranges. Data will be analyzed according to the intention to treat and per-protocol principle. In case of post-treatment dropout (i.e., patients not surviving longer than a week, or patients unable to provide pain scores and analgesic use), a worst-case analysis will be performed, where dropped-out patients will be classified as non-responders.

The domain of the primary outcome is pain response measured by the Brief Pain Inventory (BPI [28, 29]) at baseline and 14 days following the start of treatment. Pain response is defined as a reduction of pain score ≥ 2 points without an increase of analgesic intake, or a reduction of analgesic intake of ≥ 25% without an increase of pain score at the treated site. The method of aggregation is the proportion of patients with a complete or partial pain response between baseline and 14 days following the start of treatment. Differences in pain response between arms will be compared by *χ*^2^-test. We will also conduct a time-to-event analysis for pain response. Here, the method of aggregation is the median time to pain response. Survival analysis will be performed by the Kaplan–Meier estimate and is calculated as the number of subjects surviving divided by the number of patients at risk (proportion). Survival proportions will be compared at 6 months. Toxicity will be presented as the proportion of CTCAE grade 3–4 toxicity in the 6 months following the start of treatment and differences will be tested with the *χ*^2^-test. QoL will be expressed as the mean (or median) score on a scale of 0–100 (EORTC [31–35]) and compared between the three groups at 3 and 6 months after treatment starts. A mean change of 10% of the scale breadth from the baseline will be considered a clinically relevant change in QoL. We will evaluate the pattern of QoL as a continuous outcome over time using mixed models. Differences with a *P*-value of < 0.05 will be considered statistically significant. No additional subgroup analyses are planned.

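### The first scheduled QoL, EQ-5D-5L and HADS/EDIZ assessment is on the treatment day, after the patient knows the arm, so the baseline for the 10% QoL change criterion is a post-randomisation value and utility during the wait is not measured

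*Protocol article*

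**What the plan says.** Table 3 (Patient selection and follow-up) has separate columns for inclusion (Ti) and treatment (T0). Informed consent, baseline data and the "Brief Pain Inventory" are marked at Ti. The row "Quality of life questionnaires", footnoted as "EORTC QLQ BM22, EORTC QLQ C15-PAL, EQ-5D-5L", has no mark at Ti and its first mark at T0. The row that begins "Anxiety and depression in patient/partner/caregiver (HADS + EDIZ" follows the same pattern.

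Table 1, item 2.3, nevertheless promises a baseline: "Assessed using the EORTC QLQ BM22, C15-PAL, EQ-5D-5L, and PGIC at baseline; 1, 2, and 4 weeks". Item 2.5 does the same for HADS and EDIZ. The text before Table 3 adds that "patients will also be interviewed or contacted by telephone at baseline", with QoL among the purposes, but gives neither the day nor the order relative to randomisation.

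Study design places randomisation after inclusion. Intervention allocation says that nobody is blinded and that "Shortly after randomization, the patients will be informed about the randomization outcome and randomization arm-specific procedures". The legend of Fig. 2 starts follow-up after the first treatment session in all three arms.

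Statistical analysis sets the QoL criterion: "A mean change of 10% of the scale breadth from the baseline will be considered a clinically relevant change in QoL". It also compares QoL between the groups at 3 and 6 months and models QoL over time with mixed models. QALYs are to come from the EQ-5D-5L.

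**The concern.** A baseline protects an arm comparison because it cannot depend on the arm. A T0 value lacks that property. By T0 the patient knows the allocation, has waited for treatment, may have changed analgesics or dexamethasone (Analgesic medication allows this before treatment), and in the MR-HIFU arms may be facing a procedure under sedation or anaesthesia. Mood and QoL scores can respond to all of these.

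Three uses are exposed: the 10% change criterion, any model that treats T0 as a baseline, and the QALY account. The last is exposed because no EQ-5D-5L is taken during the wait. The article treats planning delay as important enough to add a pain outcome at 14 days after inclusion, and it takes an inclusion BPI. The QoL and utility instruments have no assessment at inclusion.

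**Working it through.** The article states no figure on this point to reproduce. The check is a reading of the schedule, followed by an illustration with assumed values.

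**Schedule**

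1. Order of events: inclusion (Ti), randomisation, disclosure of the arm, wait, treatment (T0). Sources: Study design, Intervention allocation, Table 3.
2. First QoL, EQ-5D-5L and HADS/EDIZ mark: T0. First BPI mark: Ti.
3. Table 1 requires a baseline for these instruments. T0 is the only scheduled assessment that precedes the follow-up visits, so it must be the baseline. It falls after step 1's disclosure in every arm.
4. Does the wait differ by arm? The Discussion calls MR-HIFU planning more complex and logistically harder than EBRT, and Objectives gives the same reason for the 14-days-after-inclusion outcome. A different wait is therefore probable, but no waiting time is given. The abstract describes the combined arm as EBRT followed by MR-HIFU. In that order its T0 is an EBRT session, and the longer wait may fall mainly on MR-HIFU alone.

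**QoL scale**

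Threshold = 10% × 100 = 10 points. Change = follow-up score − T0 score, so an arm-related shift of d points at T0 moves the change by d points. With an assumed d of 3 to 5, this is 3/10 to 5/10, or 30–50% of the threshold.

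**QALYs** (waits, utilities and gains are all assumed)

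| Quantity | Formula | Result |
|---|---|---|
| Health time outside a clock that starts at T0, for an extra wait of 3, 7 or 14 days at utility 0.5 | 0.5 × days/365 | 0.004, 0.010, 0.019 |
| Loss from the same waits if utility while waiting is 0.2 lower than after treatment | 0.2 × days/365 | 0.0016, 0.0038, 0.0077 |
| Effect of a T0 utility difference of 0.02, 0.05 or 0.10 on an unadjusted area under the curve from T0 (first-week segment only) | difference × (7/2)/365 | 0.00019, 0.00048, 0.00096 |
| Effect of the same differences if QALYs are computed as change from T0 over 6 months | difference × 0.5 | 0.010, 0.025, 0.050 |

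For scale, the 7-day loss of 0.0038 is 8% of an assumed 6-month gain of 0.05 (0.0038/0.05) and 19% of one of 0.02 (0.0038/0.02).

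The last two rows show that the effect depends on the analysis. A T0 difference hardly moves an unadjusted area under the curve, but it moves a baseline-subtracted one fully.

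**The case against.** The strongest case against is that few stated analyses use this baseline.

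- **QoL.** The comparison at 3 and 6 months is of scores, which needs no baseline. The mixed model is given no baseline covariate. The 10% rule is a benchmark for reading a mean change, not a specified arm contrast. This stands and narrows the point to the change criterion and to any model that uses T0 as a baseline.
- **HADS/EDIZ.** No change-from-baseline analysis is stated, so only the timing is shown. This stands.
- **QALYs.** The article gives no start rule, and such detail may lie in documents not shown. A reader might infer from Fig. 2 that the QALY clock starts at T0, but the article does not say so. The QALY point is therefore conditional. What is not conditional is that no EQ-5D-5L is scheduled during the wait.
- **Waiting time.** A reader might take the article to say that MR-HIFU is slower. It says only that planning is more complex and more challenging. It also asks for treatment as soon as possible and, in the combined arm, preferably within one week.
- **Coherence.** The primary endpoint and follow-up are timed from the start of treatment, and T0 fits that clock. A clock from treatment does not require the covariate to be measured then: the BPI is taken at Ti.
- **Baseline elsewhere.** The unitemised baseline data at Ti and the baseline telephone contact might include QoL. Neither names the questionnaires or places them before randomisation, and Table 3 gives these instruments their own rows, blank at Ti. This lowers certainty a little but does not remove the point.

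**Conclusion.** The point holds for the timing. The only scheduled baseline for QoL, EQ-5D-5L and HADS/EDIZ is a post-randomisation value that knowledge of the arm may affect, as may a wait that probably differs by arm. It bears on the 10% change criterion and on any analysis that treats T0 as a baseline. Utility during the wait is unmeasured and would be left out of QALYs counted from T0.

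Only secondary and economic outcomes are touched. A reader might infer that the trial's QoL comparison is biased, and by a known amount. The documents do not support this: the 3- and 6-month comparison is unaffected, and neither direction nor size of any bias can be derived. The figures above show what assumed inputs would imply and are not estimates for this trial. The point merits action because the remedy is cheap.

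**What to change.** **Patients not yet enrolled.** Add a mark at Ti in Table 3 for the patient QoL questionnaires, EQ-5D-5L and HADS, completed after consent and before randomisation, together with the BPI. Collect the partner and caregiver HADS/EDIZ at Ti where these persons attend. Define this as the baseline in Table 1 and for the 10% criterion.

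**Patients already enrolled.** Flag those with only a T0 value. Do not use that value as a pre-randomisation covariate or baseline, and do not constrain the arms to equal means at T0 in the mixed model.

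**QALYs.** State that they are counted from inclusion or randomisation, with a sensitivity analysis over plausible utilities for the unmeasured wait.

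**Cost.** There is a short added burden at the inclusion visit, and partners or caregivers may not be present. The baseline time will be mixed across patients. The article appeared on 29 December 2022 and recruitment was expected to end on 10 March 2023, so the schedule change would reach few patients. The analysis rules apply to all of them and need no new data.
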